| Background and rationale | 6a | 
Description of Research Question and Justification
 
The primary research question for this study is: "Can the act of kissing accelerate the recovery of salivary pH after consuming acidic beverages compared to the natural recovery process?"
 
Rationale for the Study:
 
This study is motivated by the increasing prevalence of dental caries worldwide, largely influenced by frequent exposure to dietary acids, which lower salivary pH and demineralize enamel. Previous studies have explored various methods to restore salivary pH, such as the use of mouth rinses, chewing gum, and dietary interventions. However, no research has yet evaluated the potential protective effect of kissing—a natural and common behavior—on salivary pH recovery.
 
Summary of Relevant Studies:
 
 
1. Acidic Beverage Impact on Salivary pH: Studies have shown that beverages like sodas and citrus-based drinks significantly reduce salivary pH, which can persist for up to 40 minutes, creating a window of susceptibility for enamel erosion and caries development.
 
2. Kissing and Salivary Exchange: Limited literature suggests that kissing facilitates salivary exchange, which may dilute acidic components and introduce buffering agents from one partner's saliva, potentially aiding in faster pH recovery.
 
3. Gaps in Current Knowledge: While previous research has focused on artificial interventions, the natural interaction between two individuals during a kiss has not been studied, leaving a gap in understanding its potential health benefits.
 
 
This study aims to address this gap by systematically evaluating the effect of kissing on salivary pH recovery, with the goal of identifying a novel, accessible, and natural protective behavior against acidic challenges to oral health.
 |

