| Outcomes | 12  | 
Primary Outcome:
 
The primary outcome of this study is the time required for salivary pH to return to neutral levels (pH ~7) after the intervention (kissing). The objective is to demonstrate that the act of kissing facilitates a faster restoration of salivary pH compared to the physiological time required in the absence of a kiss.
 
Secondary Outcomes:
 
 
1. The salivary pH level measured at each time interval during the 40-minute observation period.
 
2. Comparison of salivary pH restoration rates between: 
 
o The control group and the two experimental groups.
 
o Experimental group 1 (only one partner consumes the acidic beverage) and experimental group 2 (both partners consume the acidic beverage).
 
 
 
 
Methods of Measurement:
 
A pH meter will be used to measure the hydrogen ion activity in the saliva, reflecting its acidity or basicity. The device employs a Toledo micro combined pH electrode with the following specifications:
 
 
o Measuring range: pH 0 - 14.
 
o Temperature range: 0°C - 80°C.
 
o Shaft dimensions: 60mm length and 3mm diameter.
 
o Glass membrane: U-type with resistance <600M at 25°C.
 
o Reference system: ARGENTHAL with Ag+ ion trap.
 
 
The saliva sample will be unstimulated to avoid pH alterations caused by increased salivary flow. A small sample volume is expected, and the thin electrode design ensures accurate measurement even in reduced quantities.
 
Measurement Timeline:
 
 
1. A baseline saliva sample will be collected before the participants consume the acidic beverage.
 
2. Immediately after ingesting the beverage, a second saliva sample will be collected.
 
3. Participants in the experimental groups will kiss for 40 seconds, while the control group will wait.
 
4. A saliva sample will be collected at 5-minute intervals for the next 40 minutes, resulting in a total of nine post-intervention samples per participant.
 
 
Justification:
 
Measuring salivary pH every 5 minutes is a standard approach in similar studies assessing the dynamics of salivary pH restoration. Additionally, measuring pH immediately after consuming acidic beverages is consistent with other research protocols. Using a pH meter ensures precise and objective measurements, while collecting unstimulated saliva minimizes alterations in pH caused by increased flow rate, enhancing the reliability of the data.
 |

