| Sample size          | 14 | 
The sample size calculation was conducted using the G*Power statistical software (version 3.1.9.7, Fran Faul, Universität Kiel, Germany). The calculation was based on data obtained from the pilot study titled "Comparison of Salivary pH Changes after Consumption of Two Sweetened Malaysian Local Drinks among Individuals with Low Caries Experience: A Pilot Study". This study measured salivary pH changes after consuming acidic beverages and provided the necessary statistical parameters for sample size estimation.
 
Specifically, the following values from the pilot study were used:
 
 
Control group (mineral water): mean = 7.10, SD = 0.18.
 
Experimental group (local drink): mean = 6.86, SD = 0.18.
 
 
To calculate the effect size (<math>f</math>) for ANOVA, the means and standard deviations were combined using the formula:
 $n = \frac{(2 * (Z\beta + Z\alpha)^2 * \sigma^2)}{\Delta^2}$ 
Given the mean difference (7.10 - 6.86 = 0.24) and pooled SD of 0.18, <math>d=1.33d=1.33d=1.33</math>. Dividing by the square root of the number of groups (<math>k=3</math>), the resulting effect size was <math>f=0.76</math>, which is considered a large effect size.
 
The following input parameters were used in G*Power:
 
 
Effect size (<math>f</math>): 0.76 (large effect size based on observed data).
 
Alpha error probability (<math>\alpha</math>): 0.05.
 
Power (1-<math>\beta</math>): 0.95.
 
Number of groups: 3.
 
 
The output indicated that a total sample size of 30 participants is required to achieve a power of 95%, with 10 participants per group. To account for potential dropouts, an additional 20% will be recruited, resulting in a total of 36 participants (12 per group).
 
This effect size and resulting sample size are justified based on the observed differences in the pilot study, which measured salivary pH using similar methods (pH meter, unstimulated saliva samples in test tubes) and reported statistically significant differences between groups. Using this approach ensures that the sample size is both statistically adequate and logistically feasible for this study.
 |

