| Data collection methods                                   | 18a | 
The primary outcome of this study is the time required for salivary pH to return to neutral (pH 7.0) after the kissing intervention, compared to the control group. Baseline data, including the initial pH of unstimulated saliva before the intervention, will also be collected. Secondary outcomes include salivary pH measurements at defined time intervals (e.g., immediately after the intervention and every 5 minutes up to 40 minutes).
 
Data Collection Process:
 
 
○ Participants will expectorate saliva into sterile 3 mL conical Eppendorf tubes at each designated time point.
 
○ A calibrated pH meter will be used to measure the pH of the collected saliva. Calibration will be performed using standard buffer solutions at pH 4.01 and pH 7.01 before each data collection session, ensuring accuracy and reliability of the measurements.
 
○ All pH measurements will be conducted by trained members of the research team, who will follow a standardized protocol to minimize variability and ensure data quality. Duplicate measurements will be taken for 10% of the samples to verify consistency.
 
 
Data Recording:
 
 
○ Measured values will be entered directly into a secure, cloud-based Excel spreadsheet accessible only to authorized members of the research team. This ensures data integrity and confidentiality.
 
 |

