| Statistical methods | 20a | 
Analysis of Primary and Secondary Outcomes:
 
The primary outcome, the time required for salivary pH to return to neutral (pH 7.0), will be analyzed using appropriate statistical methods depending on the data distribution. First, tests of normality (e.g., Shapiro-Wilk test) will be conducted to determine if the data follows a normal distribution. If the data meets the assumptions for parametric tests, a one-way ANOVA will be used to compare the mean recovery times across the three groups: control, experimental group 1 (only one partner drinks the acidic beverage), and experimental group 2 (both partners drink the acidic beverage).
 
If the assumptions for ANOVA are not met, the non-parametric Kruskal-Wallis test will be applied to compare the groups. Post-hoc analyses (e.g., Tukey's HSD for ANOVA or pairwise comparisons with Bonferroni correction for Kruskal-Wallis) will be conducted to identify specific group differences.
 
For secondary outcomes, including salivary pH levels at specific time intervals, repeated-measures ANOVA will be used if the data meets parametric assumptions. Otherwise, the Friedman test will be employed to evaluate changes in pH over time within and between groups.
 
Additionally, pairwise comparisons will be performed to assess the differences in mean recovery times between the control group and each experimental group (control vs. experimental 1, and control vs.
                                                                                                                                                                                                                                                                                                                                                                                                                                                                                                                                                                                                                                                                  |

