|                            | 20b | 
Missing data will be managed using the following approach:
 
 
1. Complete-Case Analysis: Only participants with complete data for the primary outcome will be included in the primary analysis.
 
2. Sensitivity Analysis: If more than 10% of the data are missing, sensitivity analyses will be conducted using multiple imputation methods to assess the robustness of the findings.
 
3. Documentation of Missing Data: All instances of missing data will be documented, and the reasons for missingness (if known) will be recorded in a study log.
 
                                                                                                                                                                                                                                                                                                                                                                                                                                                                                                                                                                                                                                                                                                                                                                                                                                                                                                                                                                                                                                                                                                                                                                                                                                                                                                                                                                                                              |

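### Time to pH 7.0 is cut off at 40 minutes, but the complete-case comparison of recovery times gives no rule for participants still below 7.0, who on the natural reading are excluded because of their outcome

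*Protocol*

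**What the plan says.** All references are to numbered items of the protocol.

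- **Outcome.** Item 12 defines the primary outcome as the "time required for salivary pH to return to neutral levels (pH ~7"), with no tolerance. Items 18a and 20a give the target as exactly 7.0.
- **Window.** Item 12 samples saliva every 5 minutes. A secondary outcome is pH "measured at each time interval during the 40-minute observation period".
- **Test.** Item 20a says "a one-way ANOVA will be used to compare the mean recovery times across the three groups", with Kruskal-Wallis if the assumptions fail.
- **Missing data.** Item 20b says "Only participants with complete data for the primary outcome will be included in the primary analysis". Multiple imputation is a sensitivity analysis, run only if more than 10% of the data are missing.
- **Expected duration.** Item 6a says that acidic drinks "significantly reduce salivary pH, which can persist for up to 40 minutes", which is the whole observation window.
- **Baseline.** Item 18a says "Baseline data, including the initial pH of unstimulated saliva before the intervention, will also be collected". Item 10 requires no minimum pH for entry, and the target does not refer to the participant's own baseline.

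No item gives a censoring rule, a time-to-event method, or a value to assign to a participant who is still below 7.0 at the last sample.

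**The concern.** Recovery time is a time to an event, seen on a 5-minute grid and cut off at 40 minutes. A participant below 7.0 at the last sample has not lost data: the recovery time is known to exceed 40 minutes. A comparison of mean times has no number to use for that person, and the complete-case rule then removes them.

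That removal depends on the outcome. If kissing speeds recovery, more controls than kissers are removed, and the controls who remain are the faster ones. The groups analysed are no longer the groups randomised, and the difference in recovery time tends to shrink.

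The multiple-imputation step does not reliably repair this. It does not touch the primary analysis and has a trigger. Unless the imputation model is told that the missing times exceed 40 minutes, it may borrow times from those who recovered.

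A related but separate problem is the fixed target. A participant whose resting pH is below 7.0 can return fully to their own baseline and still register no recovery.

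**Working it through.** **1. The plan's own figure.** Item 14 gives a total of 30 for a one-way ANOVA with k = 3, f = 0.76, alpha 0.05 and power 0.95. The noncentrality is f² × N = 0.76² × 30 = 17.3, and the noncentral F power is 0.950. The figure reproduces. It presumes that all 30 contribute an outcome value.

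**2. What happens to a non-recoverer.** Reading items 12, 20a and 20b together:

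- Below 7.0 at every sample to 40 minutes: no observed recovery time.
- No recovery time: nothing to enter into a mean.
- No value for the primary outcome: outside the complete-case set, on the natural reading.

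The alternative is that a full pH series counts as complete data. Then item 20a still lacks a value for that person, and one would have to be chosen after the data are seen.

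**3. Direction and possible size of the bias.** The documents give no distribution of recovery times, so this is an illustration. Assume lognormal times with log-SD 0.5, medians of 30 minutes (control) and 20 minutes (kissing), read at the next 5-minute sample.

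- No recovery by 40 minutes, control: 1 − Φ(ln(40/30)/0.5) = 1 − Φ(0.575) = 28%.
- No recovery by 40 minutes, kissing: 1 − Φ(ln(40/20)/0.5) = 1 − Φ(1.386) = 8%.
- Mean recorded time among those who recovered: 27.6 and 22.6 minutes, a complete-case difference of 5.0.
- Everyone kept, non-recoverers counted as 40 minutes: 0.717 × 27.56 + 0.283 × 40 = 31.1, and 0.917 × 22.55 + 0.083 × 40 = 24.0, a difference of 7.1.
- Untruncated mean difference: (30 − 20) × e^0.125 = 11.3 minutes, which a 40-minute window cannot estimate without a model.

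Other assumed medians gave the same direction:

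| Median, control / kissing (min) | Untruncated difference | Complete-case difference |
|---|---|---|
| 20 / 15 | 5.6 | 3.9 |
| 30 / 15 | 17.0 | 8.8 |
| 40 / 20 | 22.6 | 7.8 |

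With equal medians in the two groups the complete-case difference was 0.0.

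**4. The fixed target.** The protocol states no resting pH. Its nearest figure is the cited pilot study's entry in item 14, "Control group (mineral water): mean = 7.10, SD = 0.18". Assume that this approximates resting pH and that pH is normal.

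- P(pH < 7.0) = Φ((7.00 − 7.10)/0.18) = Φ(−0.556) = 28.9%.
- With the SD assumed to be 0.10: Φ(−1.00) = 16%. With 0.30: Φ(−0.333) = 37%.
- If the approximate target in item 12 means 6.9: Φ((6.90 − 7.10)/0.18) = Φ(−1.11) = 13%.

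In numbers, 0.289 × 36 = 10.4 of the 36 participants in item 14, or 0.289 × 45 = 13.0 of one drinker from each of the 45 couples in item 2b. If all were excluded from the 36, about 26 would remain, fewer than the 30 that item 14 requires.

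**The case against.** The strongest reply is that item 20b concerns missing data, and a participant who gives every scheduled sample has no missing pH. The text never says that non-recoverers are dropped. Assigning them 40 minutes or more and using Kruskal-Wallis, which item 20a allows, fits the wording, and a censoring convention is often left to an analysis plan. Part of this stands: exclusion is an inference and should be described as one. But the protocol does fix the test and the analysis set, and neither provides for an outcome that its own background section makes foreseeable. Fixing a complete-case comparison of recovery times for a censored outcome is a poor choice of method, not only missing detail.

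A reader might also infer that, by the plan's own figures, 29% of participants have a natural pH below 7.0. The documents do not support that. The figure comes from the mineral-water arm of an outside pilot, is used only for sample size, and is never called resting pH.

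Nor does a low resting pH show that the slowest recoverers are discarded. Someone resting at 6.95 may be back there in 5 minutes. For that person the target is unattainable; recovery is not slow. Censoring or worst-ranking alone would still score that person as slow.

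Finally, a reader might infer that the plan roughly halves the power. Simulations with 15 per group, assumed baselines as in step 4 and an assumed exponential return to baseline do not settle it:

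| Assumed pH drop; time constants, control vs kissing | Power, recovered only | Power, worst rank |
|---|---|---|
| 1.0; 20 vs 10 min | 29% | 51% |
| 0.24; 20 vs 10 min | 6% | 7% |
| 1.0; 10 vs 5 min | 49% | 39% |

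A gain, almost no change and a reversal all occur, so no single power figure can be attached to this point.

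The pH values at each time point do remain as secondary outcomes, so the trajectories of non-recoverers are not lost to the trial. That does not repair the primary analysis.

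**Conclusion.** The point holds as two linked problems.

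First, the primary outcome is right-censored at 40 minutes, and the plan pairs a comparison of recovery times with a complete-case rule and no provision for non-recovery. On the natural reading this selects participants by their outcome, breaks the randomised comparison and tends to understate a real difference. The direction was the same in every illustration of the difference in recovery times where the groups differed. The size (5.0 against 7.1 minutes in the worked case) rests on assumed distributions.

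Second, the target ignores the participant's own baseline. About 29% might be unable to reach 7.0, conditional on normality and on the pilot's mineral-water arm standing in for resting pH. The range is 16% to 37% over the assumed SDs, and 13% at a cut-off of 6.9.

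The documents do not establish that non-recoverers are expressly dropped, that the second problem causes the first, or that power is lost by a particular amount. The issue should be settled before enrolment because it decides who enters the primary analysis.

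**What to change.** In items 20a and 20b, state that:

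- every randomised drinker with a pH series is in the primary analysis;
- a participant below 7.0 at the last sample is censored at 40 minutes and is not treated as missing;
- the groups are compared by a log-rank test or an interval-censored model, since recovery is known only to lie between two consecutive samples, or by Kruskal-Wallis with non-recoverers tied at the worst rank;
- the comparison is adjusted or stratified for baseline pH where the method allows;
- the complete-case rule applies only to samples that were truly lost.

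Make items 12, 18a and 20a agree on whether the target is exactly 7.0 or has a stated tolerance. Add a sensitivity analysis that defines recovery relative to the participant's own baseline. The registered endpoint should stay as the primary one, because replacing it would change what the trial estimates and any tolerance around baseline would have no source in the protocol.

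The cost is protocol wording, with the ethics submission and registry update that item 25 requires for a change to the analysis. No new samples are needed, since the baseline and the 5-minute series are already planned, and item 2b lists the trial as not yet recruiting.

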**Figure 1. Schedule of Enrolment, Interventions, and Assessments**

| Study Period                    | Enrolment | Allocation | Post-Allocation | Close-Out |
|----------------------------------------|------------------|-------------------|------------------------|------------------|
| Timepoint                       | Week 1-2         | Week 3            | Week 3-10              | Week 11-12       |
| Enrolment:                      |                  |                   |                        |                  |
| - Eligibility screening                | X                |                   |                        |                  |
| - Informed consent                     | X                |                   |                        |                  |
| - Baseline assessments                 |                  | X                 |                        |                  |
| Interventions:                  |                  |                   |                        |                  |
| - Group Experimental 1                 |                  |                   | X                      |                  |
| - Group Experimental 2                 |                  |                   | X                      |                  |
| - Group Control                        |                  |                   | X                      |                  |
| Assessments:                    |                  |                   |                        |                  |
| - Immediate post-intervention          |                  |                   | X                      |                  |
| - Follow-up (every 5 min up to 40 min) |                  |                   | X                      |                  |
| Data Analysis:                  |                  |                   |                        | X                |

## Appendices 2. Plan for Handling Biological Specimens

Below is a detailed plan for handling biological specimens (saliva) collected during the study. This document is prepared to comply with institutional and international ethical guidelines and can be included as an appendix to the protocol.

---

### Plan for Handling Biological Specimens: Saliva Samples

#### 1. Collection of Samples:

- Saliva samples will be collected from participants using **sterile, 3 mL conical Eppendorf tubes**.
- Samples will be collected at predefined time intervals:
  - Before consuming the assigned beverage (baseline).
  - Immediately after consuming the beverage.
  - At regular intervals following the intervention (e.g., every 5 minutes).
- Unstimulated saliva will be collected to avoid altering the natural pH.

